### Determination of the counterfactuals for comparison

Since there is no enrolled comparison group in this study, the counterfactuals to be included to determine how effective BBM is will be threefold:Versus similar New Zealand population. The estimated mean weight change of ethnic/gender/age groups will be derived from the last five years of NZ Health Surveys [15] and these will be compared with the general programme groups participating in BBM. Note that, longitudinally, weight change in a subpopulation is the additive effects of secular changes to weight (ie each age group gets a little heavier each year) and age-related weight change (ie the person moves to an older age group which has a higher average weight).Versus control groups in other similar studies. A literature review [16] has identified five weight loss studies with predominantly Pacific or Māori participants that had control groups (total *N* = 955, follow-up 3–24 months) [17–21]. Their weight change trajectories will be compared to the BBM general programme participants.Versus other interventions. The literature review noted above [16] identified 18 studies with various interventions with weight change outcomes [17–34]. These combined results show how effective other programmes have been. Since the duration of interventions varies (3–24 months), weight loss is not linear.

A mixed method meta-analysis was conducted using the metaphor package [35] in R. Studies were only included in this analysis where the difference with baseline (time 0) was published together with their standard error, standard deviation, or confidence interval (to enable calculation of the standard error). Figure 1 shows the forest plot of the included studies.

**Fig. 1 Fig1:**
[figure not shown]
Forest plot of effect size and confidence intervals for controls and interventions in the included studies

The moderator variables were intervention, time, and interaction intervention and time, and the response variable was the weight change in time from a baseline of zero for both control and intervention. The random variable was the interaction between the individual studies and the intervention. Spline functions are formed by joining polynomials together at fixed points called knots*.* The number and position of knots in the spline function was found by evaluating the Akaike Information Criterium (AIC) using all possible combinations of placement of two knots [36]. The best AIC was found with one knot at two months. Splines were compared with polynomials, but the fit of a spline function was superior to them. A spline function with one knot could be fitted within a mixed effects meta-analysis to describe the initial weight loss followed by increase in weight (Fig. 2).

**Fig. 2 Fig2:**
[figure not shown]
Weight change in kilograms against time in months for each study in the meta-analysis

A funnel plot of the standard errors against the residual values after fit was symmetrical, with a non-significant Eggers test (*p* = 0.8505), indicating no evidence of publication bias in the articles used in the meta-analysis (Fig. 3).

**Fig. 3 Fig3:**
[figure not shown]
Forest plot of the standard errors from the studies used in the meta-analysis

Weight for both the general BBM and the FTC cohorts will be analysed as with a general linear mixed model for repeated measures, with person (participant) as the random variable and time as the fixed variable. The two cohorts will be combined because some general BBM members may previously have been FTC participants, and some FTC participants subsequently become general members. The weights will be logarithmic transformed before analysis, if the residual analysis indicates that. The comparison of our study data with the tick shaped curve prediction model generated from the literature (Fig. 2) will be done by comparing specific points in time and calculating the t-probability of being equal on basis of their 95% confidence intervals.

The FTC group will be considered as a series of three cohorts of about 20 participants each entering the FTC programme. An estimate of 80% recruitment into the study will give 50 participants who will have baseline and follow up data. There is also no parallel comparison group for this part of the study. However, their weight change trajectories can also be compared with the counterfactuals noted above. FTC data will be analysed with a Difference in Difference (DID) analysis using the estimated covariance matrix from the repeated measures analysis to obtain the corrected differences (Treatment – Baseline) – (Control – Baseline) as an estimate of the effect of the programme.

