### Statistical analysis

All statistical analysis will be done in R [13] using the lme4 package [14]. The primary outcome of interest is sustained weight loss. How successful BBM is at helping participants lose and maintain 5% weight loss will be a critical outcome measure, however, the effectiveness of BBM compared to other counterfactuals will also be assessed.

The general programme cohort will include existing and new entrants. For existing members we will also have self-reported weights at their first BBM session, which will be considered the baseline or ‘time zero (T0)’ weight with subsequent times measured from then. For example, for a person who started at BBM seven months before enrolment in the study, their reported weight at BBM entry will be T0, their enrolment weight (measured by the research team at study enrolment) will be T7, their 6-month weight will be T13, 24-month weight will be T31. Typically, the pattern of weight loss with weight loss programmes is tick-shaped with a weight loss nadir at 6–12 months followed slow return back towards T0 weight or beyond. Estimated duration of the study will be 24 months of follow-up from enrolment.

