Obesity is the consequence of complex, adaptive, societal systems and therefore approaches to deal with obesity (treatment or prevention) need to use systems tools to manage that complexity [8]. There is a lack of evidence implementing systems-level thinking and analyses to evaluate and assist in the evolution of a community programme delivering health and wellbeing services for Pacific and Māori people which uses culturally appropriate methods of inquiry [38]. The partnership of BBM and University of Auckland researchers are exploring the evidence base for BBM using kaupapa Māori and co-design [39], with the aim of improving health outcomes and reducing health inequities [40, 41]. The Pacific approaches of fa’afaletui [42, 43] and fonofale [44], and the similar te whare tapa whā model [45] use an empowerment rather than a deficit model, with a holistic view of physical, mental, spiritual and family / community health in the context of people’s lives.

Our participants are willing partakers of the BBM programme, who have joined to make a change in their health status and lives going forward. Their motivation to engage in research that aims to improve health and wellbeing has been demonstrated in our prior qualitative investigation. Combining indigenous cultural frameworks in the delivery of health support services may prove critical for sustained engagement, and significantly improved outcomes for Pacific and Māori populations.

While a pragmatic before-after study design has no control group, there is very strong evidence that a non-intervention counterfactual of no weight change is plausible, since the average natural trajectory of people with obesity is no change or slow increases in weight. A sustained weight loss of 5–10% is clinically meaningful for health benefits, even if people remain overweight or even obese [2].

Inevitably, the COVID-19 pandemic adds additional challenges. Recurrent Alert Level 4 and 3 lockdowns, the latest in August to October 2021, has delayed initial recruitment. It may be several months before the city is again at Alert Level 1 and full social gatherings can be resumed, including BBM bootcamps. In the interim, BBM provides online classes via their social media platform, as well as distributing hundreds of parcels of donated healthy food daily to vulnerable and socioeconomically disadvantaged members experiencing food insecurity through the financial stresses imposed by the lockdown.

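### The one test spelled out against the literature is an equality test on a curve whose arm is not named, and the curve's description points to other weight-loss programmes rather than to no programme

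*Protocol article*

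**What the plan says.** All references are to the protocol article.

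- **Comparators.** Under Determination of the counterfactuals for comparison, the article says that "the counterfactuals to be included to determine how effective BBM is will be threefold". They are the similar New Zealand population (from health surveys), the control groups of five studies (total N = 955), and the interventions of 18 studies. The first two represent no programme; the third represents other programmes. For the first two the article says that a comparison will be made, but gives no contrast or test.
- **The prediction model.** In the same section, the meta-analysis is described as fitted to control and intervention arms, with intervention, time and their interaction as moderators. Its one-knot spline is said "to describe the initial weight loss followed by increase in weight".
- **The test.** After Fig. 3, the reference is set in the sentence that begins "The comparison of our study data with the tick shaped curve prediction model generated from the literature (Fig. 2) will be done by comparing specific". That sentence ends by naming the method: a t-probability of equality, worked out from the two 95% confidence intervals at times that are not named.
- **What tick-shaped means.** Under Statistical analysis: "Typically, the pattern of weight loss with weight loss programmes is tick-shaped with a weight loss nadir at 6–12 months".
- **The no-programme argument.** The Discussion defends the uncontrolled design on the ground that "there is very strong evidence that a non-intervention counterfactual of no weight change is plausible".

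**The concern.** The three comparators answer two different questions: whether BBM does better than no programme, and how it compares with other programmes. An equality test means something different for each. Against a control curve, a significant result in favour of BBM supports effectiveness. Against an intervention curve, a non-significant result could come from a programme that works as well as the others or from an imprecise estimate, and a significant result could come from a programme that does not work at all.

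The test is written for one curve, in the singular, and the only description of that curve is a shape that the article attributes to weight-loss programmes. It is not the no-programme course, which the Discussion describes as stable or slowly rising weight. Taken literally, the one specified test therefore does not address the no-programme comparison, and the two comparators that do address it have no stated contrast. At stake is how the counterfactual results will be read. The same BBM data could support opposite statements depending on a choice of curve made after the data are seen.

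**Working it through.** **Step 1: which curve does the text point to?**

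| Place in the article | What it implies |
|---|---|
| Statistical analysis | Tick-shaped is the pattern of weight-loss programmes |
| Text before Fig. 2 | The spline describes loss, then regain |
| Same paragraph | Control and intervention arms are both in the model, with an interaction with time, so two curves can be predicted |
| Text after Fig. 3 | One tick-shaped curve is tested; no arm is named |
| Discussion | The no-programme course is no change or slow gain |

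The wording leans towards the intervention curve but does not fix it. Fig. 2 is not available to this review and may show both curves.

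**Step 2: does the choice change what the test means?** The article gives no curve value, standard deviation, standard error or alpha, so there is no figure of its own to reproduce on this point. The inputs below are assumptions for illustration:

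- programme curve: 3 kg loss; control curve: 0 kg (the Discussion's no-change argument)
- standard error (SE) of the difference between BBM and the curve: 0.5, 1.0 or 1.5 kg
- two-sided alpha 0.05, normal approximation

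For a true difference d, P(reject) = Φ(d/SE − 1.96) + Φ(−d/SE − 1.96).

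| True BBM loss | Tested curve | d (kg) | SE 0.5 | SE 1.0 | SE 1.5 |
|---|---|---|---|---|---|
| 3 kg | programme | 0 | 5% | 5% | 5% |
| 3 kg | control | 3 | >99% | 85% | 52% |
| 0 kg | programme | 3 | >99% | 85% | 52% |
| 0 kg | control | 0 | 5% | 5% | 5% |

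The pattern reverses. Against the programme curve, a programme that works as well as the others is rarely significant, and one with no effect is often significant, because it is worse than the curve.

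**Step 3: can a loss of power be stated?** Take a true BBM loss of 5 kg, SD of change 8 kg, 500 people weighed, and a curve SE of 0.75, 1.0 or 1.5 kg (all assumed). Then SE = √(8²/500 + SE_curve²) = √(0.128 + SE_curve²) = 0.83, 1.06 or 1.54 kg.

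| Tested curve | d (kg) | SE 0.83 | SE 1.06 | SE 1.54 |
|---|---|---|---|---|
| Control, 0 kg | 5 | >99.9% | 99.7% | 90% |
| Programme, 1 kg loss | 4 | 99.8% | 96.5% | 74% |
| Programme, 3 kg loss | 2 | 67% | 47% | 25% |
| Programme, 5 kg loss | 0 | 5% | 5% | 5% |

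At equal precision the drop from control to programme curve runs from almost nothing (1 kg, SE 0.83) to about 95 points (5 kg, SE 0.83). The control curve rests on fewer studies and is probably less precise. If it has SE 1.54 and the 3 kg programme curve has SE 0.83, the comparison is 90% against 67%, a drop of 23 points. No single figure follows from the article.

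**The case against.** The strongest reply has four parts.

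1. *The primary hypothesis does not use this test.* The Aim and objectives section sets it as an average sustained loss of at least 5% of baseline weight. Statistical analysis treats that as a critical outcome and adds the counterfactuals as a further assessment. This stands. The mixed model estimates change over time without any literature curve, and under the Discussion's no-change argument that change is itself a comparison with no programme.
2. *The tested curve is not shown to be the intervention curve.* The prediction model contains control arms, and Fig. 2 cannot be inspected. This stands as well. It turns the point from a wrong comparator into an unnamed one, but an equality test whose reference arm is unnamed still has no fixed meaning.
3. *No-programme comparisons are planned.* The health-survey and control-group comparisons are listed, and the FTC analysis has a difference-in-difference with a control term. True. However, the first two have no stated contrast, and the FTC control term has no named source, with no parallel comparison group and about 50 participants.
4. *Details of this kind belong in a fuller document.* That would answer a complaint of silence. Here the article does state a test and a reference curve, and the difficulty lies in what it states.

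A reader might infer that the plan never asks whether BBM works compared with no programme, or that power falls by a known large amount. The article supports neither. The first is contradicted by the planned comparisons and the baseline hypothesis. The second depends entirely on assumed curve values and on the precision given to each curve.

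**Conclusion.** The point holds in a limited form. The one probability test spelled out against the literature is an equality test on a curve whose arm is not named and whose description fits weight-loss programmes. If the intervention curve is used, a non-significant result shows neither effectiveness against no programme nor equality with other programmes, and a significant result can come from an ineffective programme. The two no-programme comparators are planned without a stated contrast.

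The defect affects how the counterfactual comparison is interpreted, not the primary hypothesis. Its numerical size cannot be determined: the probabilities shown rest on assumed curve values, standard errors and a 5% two-sided level. The reversal in meaning between the two curves does not depend on those particular values; it needs only that the curves differ.

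There is also no ground in the article for insisting that the control comparison be ranked as primary. It is enough that the two contrasts are defined and kept apart.

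**What to change.** In the weight-analysis paragraph after Fig. 3, replace the equality test with two contrasts at 12 and 24 months, reported separately:

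- (a) BBM change minus the predicted control-arm change, as the estimate of effect against no programme;
- (b) BBM change minus the predicted intervention-arm change, as the comparison with other programmes.

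Give each as a difference with a 95% interval that includes the prediction model's uncertainty as well as that of the BBM estimate, for example from SE = √(SE_BBM² + SE_curve²). State that a non-significant (b) will not be read as equal effectiveness.

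The cost is one paragraph of wording. Both predictions come from the meta-regression already fitted, and no new data are needed. The drawback is that the control curve rests on at most five studies (total N = 955), so the interval for (a) is likely to be wider than that for (b).

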### Participant recruitment

For the general programme, participants will be recruited through study advertisements on BBM’s social media platforms, and as posters in physical locations (the exercise centres). BBM trainers will promote the study to BBM attendees. All attendees over the age of 16 years will be eligible to participate.

For FTC group participants, all people registering for three 12-week programmes will be invited to enrol in the study. All FTC participants will be eligible, with the exclusion of repeat attenders already enrolled in the study.

Participants from both the general and FTC groups will be offered a koha (gift) of a $40 token at the 24-month follow-up. Participants will continue to be enrolled until the target samples are reached. Given recurrent lockdowns and restrictions on class sizes due to COVID-19, it is anticipated that the study will be extended by one year to enable 24 month follow-up of all participants.

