### Sample size calculations

The study has a finite population and has a quasi-experimental design of an existing intervention with no randomised sample, hence our sample size needs to take a pragmatic approach. We will recruit a many eligible participants as possible in the available timeFor the general group the target is to recruit 1000 BBM members, and for FTC. there are about 20 enrolees in each FTC programme, and some repeat the cycle, so the total number is estimated to be about 50 over three cycles.

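### The FTC sample of 50 is reached by two different single deductions from the same 60 entries; applying both gives about 40 recruited from three cycles

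*Protocol article*

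**What the plan says.** Sample size calculations puts enrolment at roughly 20 per programme and bases the FTC number on repeat attendance: "so the total number is estimated to be about 50 over three cycles". No consent rate appears there.

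The closing text of the statistical analysis (after Figure 3, under Determination of the counterfactuals for comparison) starts from the same source: "The FTC group will be considered as a series of three cohorts of about 20 participants each entering the FTC programme". It then applies a consent rate: "An estimate of 80% recruitment into the study will give 50 participants who will have baseline and follow up data". Repeat attendance is not mentioned in this derivation.

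Participant recruitment defines who can enter. For FTC, the invitation is broad: "all people registering for three 12-week programmes will be invited to enrol in the study". Eligibility is then limited, "with the exclusion of repeat attenders already enrolled in the study". The same section adds, for the study as a whole, "Participants will continue to be enrolled until the target samples are reached".

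Aim and objectives gives the FTC sub-cohort as n ~ 50 and sets FTC data collection at programme start and at one and two years.

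**The concern.** Two passages start from about 60 entries and finish at 50, one by removing repeaters and the other by removing people who do not consent. These are separate losses. The eligibility rule makes the first apply to the study sample, and the 80% is the protocol's own estimate of the second. If both apply, neither derivation supports 50.

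The second derivation also moves straight from recruitment to having follow-up data. It does not say whether that means the end of the 12-week programme, 12 months or 24 months, and it makes no allowance for loss.

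At stake is the only size given for the second research question, which concerns sustained benefit in people with Class 3 or 4 obesity. A reader would plan around, and judge the results against, a number that the described recruitment does not produce.

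**Working it through.** **Inputs**
- Cycles: 3; entries per cycle: about 20 (Sample size calculations; Statistical analysis).
- Unique people after allowing for repeaters: about 50 (Sample size calculations).
- Recruitment rate: 80% (Statistical analysis).
- Repeat attenders already enrolled are excluded (Participant recruitment).

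**The plan's own figures**
- Entries: 3 × 20 = 60.
- Statistical analysis alone: 60 × 0.80 = 48, stated as 50. With inputs given as about 20, this reproduces.
- Sample size calculations alone: 60 entries become about 50 people, which implies 60 − 50 = 10 repeat entries (10/60 = 17%). The document does not state this count.

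**Both deductions together**
- (60 − 10) × 0.80 = 40, which is 20% below 50.
- The exclusion covers only repeaters already enrolled. If the 10 repeat entries come from people with the same 80% consent rate, 10 × 0.20 = 2 were not enrolled the first time. Inviting them again at 80% adds 2 × 0.80 = 1.6, giving 41.6, or about 42.

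**Sensitivity to the inferred repeat count**, as (60 − r) × 0.80, without re-invitation:

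| Repeat entries r | Recruited |
|---|---|
| 0 | 48 |
| 5 | 44 |
| 10 | 40 |
| 15 | 36 |

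On the stated inputs the ceiling is 48, with no repeaters at all.

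**What 50 would need**
- At 80% recruitment: 50 / 0.80 = 62.5 unique registrants.
- At 50/3 = 16.7 unique people per cycle: 62.5 / 16.7 = 3.75 cycles, so in practice a fourth.

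**Effect on precision**, with interval width proportional to 1/√n:
- n = 40 against 50: √(50/40) = 1.118, about 12% wider.
- n = 42 against 50: √(50/42) = 1.091, about 9% wider.

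**Follow-up.** The document gives no attrition rate. Purely as an illustration, assumed losses of 10% to 40% would leave 36 to 24 of 40.

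**The case against.** The strongest reply is that these are rough figures for a pragmatic sample and that nothing rests on them. The 80% derivation reproduces within two participants, and no power, standard deviation or interval width is stated for FTC. This stands as far as it goes: 48 against 50 is rounding. It does not cover 40 against 50, where a whole deduction is left out.

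A second reply is that enrolment continues until the targets are reached, and a one-year extension is expected. A reader might therefore call 50 a target that will be met, or, ignoring this rule, might conclude that 50 cannot be reached. The document supports neither. Three passages tie FTC recruitment to three programmes, and no fourth is mentioned, so the two statements need reconciling.

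A third reply is that the 50 under Sample size calculations may already include consent. The passage does not say that everyone consents, and that should not be read into it. But if consent were included, repeaters and refusals together would remove only 10 of 60, while 20% refusal alone removes 12.

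On follow-up, a reader might infer that the plan assumes no loss at 24 months. The sentence does not say that: it names no time point, FTC participants also have pre- and post-programme weights, and their clinical outcomes come from medical records that need no return visit. What remains is that the number recruited is presented as the number followed up, with the follow-up undefined.

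**Conclusion.** The FTC size is derived inconsistently. On the protocol's own inputs and its exclusion of enrolled repeaters, three cycles give about 40 recruited, or about 42 with re-invitation of those who first declined, against a stated 50. The exact shortfall depends on the inferred 10 repeat entries; its direction does not, since even with none the figure is 48.

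From the document's figures the consequence is an interval about 12% wider at 40 than at 50. This is a root-n approximation: FTC weights are to be fitted in a mixed model together with the general cohort, so it indicates the scale rather than the planned standard error. A reader might go further and quote interval widths in kilograms or a 24-month analysable number. Those would need a standard deviation and an attrition rate that the document does not give. No stated power or precision claim is broken, because none is made for FTC.

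**What to change.** Replace the two derivations with one chain used throughout: about 60 entries over three cycles, about 50 unique people, about 40 consenting, with the assumed repeat and consent rates stated. Then take one of two routes:

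- restate the FTC size as about 40, in Sample size calculations, in the statistical analysis text and at the n ~ 50 in Aim and objectives; or
- keep 50 and say that FTC recruitment will go beyond three programmes, so that the three-programme limit agrees with the continue-until-target rule.

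In either case, name the follow-up time point to which the number refers and separate the number recruited from the number expected to have data then. If a retention rate is used, mark it as an assumption.

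The cost is wording only. Under the first route a published number becomes less favourable; under the second, the team commits to about one more cycle. The analysis methods do not change.

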BBM was set up in 2014 and, by September 2021, there were over 15,000 members who variably participated in several programmes including 34 weekly free community bootcamps. BBM also offers a 12-week ‘From the Couch’ (FTC) programme, which is a highly supportive, holistic, physical activity and tailored diet programme designed for individuals who are usually morbidly obese and have very restricted physical capacity, such as not being able to ‘get off the couch or who struggle to stand for very long periods of time’. The FTC programme aims to enable individuals to move ‘from the couch’ towards eventually being able to do everyday activities, which most able-bodied people take for granted.

The BBM programme warrants a full evaluation not only to measure its social and health impacts, but to understand its internal dynamics, values and strengths to inform continuous programme improvement and increase reach and effectiveness [8]. A preliminary qualitative study using the Fonofale Pacific framework of inquiry [9] has explored the lived experience of Pacific and Māori clients and trainers. A further study is underway to conduct a process evaluation of BBM’s community engagement through its in-person, social and news media outreach activities with respect to the health and wellbeing of Pasifika and Māori people in their community over time. The underlying sociocultural values that determine sustained motivation, engagement and impact, and how these are associated with biomedical outcomes needed to be researched.

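### The From the Couch cohort may be compared with counterfactuals that are not indexed on starting weight or BMI, so a kilogram difference could reflect heavier starting weight and not programme effect

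*Protocol article*

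**What the plan says.** The section on determination of the counterfactuals sets up three benchmarks.

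1. **National health survey.** "The estimated mean weight change of ethnic/gender/age groups will be derived from the last five years of NZ Health Surveys", and "these will be compared with the general programme groups participating in BBM". No weight or BMI stratum is mentioned.
2. **Control arms of five published studies.** "Their weight change trajectories will be compared to the BBM general programme participants".
3. **Other interventions.** The literature review "identified 18 studies with various interventions with weight change outcomes". No BBM cohort is named as the one to be compared.

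The literature curve is reported as already fitted. "The moderator variables were intervention, time, and interaction intervention and time". Its response is change from a baseline of zero, and Figure 2 is captioned in kilograms. Study data are to be compared with this curve at chosen time points, with a t-probability derived from the 95% confidence intervals.

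The FTC programme is "designed for individuals who are usually morbidly obese and have very restricted physical capacity" (Background). Aim and objectives describes its members as having Class 3 or 4 obesity, BMI above 35 kg/m². The general programme has no BMI criterion (Participant recruitment). In the text after Figure 3 the article says of FTC: "There is also no parallel comparison group for this part of the study". It continues: "However, their weight change trajectories can also be compared with the counterfactuals noted above". A difference-in-difference contrast for FTC follows. It subtracts baseline from each term but does not divide by it.

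**The concern.** Two of the three benchmarks are expressly built for the general programme. The third names no cohort, but it too has no term for starting weight. All three are then made available for a group selected for severe obesity, and nothing in the article matches, restricts or adjusts any of them to that group.

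A curve in kilograms with no baseline-weight term predicts the same loss for a cohort averaging 100 kg as for one averaging 150 kg. If loss is roughly proportional to weight, the heavier cohort will appear to outperform other programmes when it is equally effective. Against control arms the bias could run the other way: if untreated people gain in proportion to their size, a gain taken from lighter controls is too small and FTC's benefit is understated. In either direction, the difference between FTC and the benchmark could not be read as a programme effect.

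**Working it through.** **The plan's own FTC number.** Three cohorts of about 20 at 80% recruitment: 3 × 20 × 0.80 = 48, against a stated 50. This agrees to within rounding of the word about. The article states no alpha, power, SD or effect size for this comparison, so there is no power figure to reproduce.

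**What the benchmarks condition on**

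| Benchmark | Indexed on | Cohort named |
|---|---|---|
| Health survey | ethnicity, gender, age | general programme |
| Control arms | predominantly Pacific or Māori; time | general programme |
| Other interventions | intervention, time, their interaction | none |

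None carries weight or BMI. The mixed model for the study weights has time as its only fixed effect and combines the two cohorts, so it supplies no adjustment either. The log transformation is conditional on residuals and is mentioned for the study weights, not for the literature curve.

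**Assumptions for the illustration (none is in the documents).** Literature mean weight 100 kg; FTC mean W = 120, 135 or 150 kg; the same percentage loss p in both; SD of change s = 5% or 7% of weight; curve SE 0.3 kg; n = 50; two-sided 5% test, hence 2.5% in FTC's favour. For orientation, at a height of 1.70 m a BMI of 35 is 35 × 1.70² = 101 kg and a BMI of 45 is 130 kg.

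**Formulas**

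- Artefact: d = p × (W − 100)
- SE = √[(s × W)²/n + 0.3²]
- Chance of a spurious result favouring FTC = Φ(−1.96 + d/SE)

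**Worked cases, p = 3%**

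- W = 120, s = 7%: d = 0.03 × 20 = 0.60 kg; SE = √(8.4²/50 + 0.09) = 1.225; Φ(−1.96 + 0.490) = 0.071.
- W = 135, s = 7%: d = 1.05 kg; SE = √(9.45²/50 + 0.09) = 1.370; Φ(−1.96 + 0.766) = 0.116.
- W = 150, s = 5%: d = 1.50 kg; SE = √(7.5²/50 + 0.09) = 1.102; Φ(−1.96 + 1.361) = 0.27.

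**Range over s = 5% to 7%**

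| Equal loss | 120 kg | 135 kg | 150 kg |
|---|---|---|---|
| 3%: artefact | 0.6 kg | 1.05 kg | 1.5 kg |
| 3%: chance | 7-10% | 12-18% | 17-27% |
| 5%: artefact | 1.0 kg | 1.75 kg | 2.5 kg |
| 5%: chance | 13-20% | 25-42% | 38-62% |

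**Sensitivity.** At p = 2% and 120 kg the chance is 5-6%. At p = 3% and 135 kg, raising the curve SE to 0.6 kg gives 11-15%, and to 1.0 kg gives 9-12%.

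**On a percentage scale** the artefact is p − p = 0, so everything quantified here disappears.

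**If the test uses the combined cohorts.** With recruitment targets of 1000 and 50, FTC is 50/1050 = 4.8% of participants. The 1.05 kg artefact becomes 1.05 × 0.048 = 0.05 kg. With s × 100 kg = 5 kg, SE = √(5²/1050 + 0.09) = 0.337, and the chance is Φ(−1.96 + 0.05/0.337) = about 3.5%.

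**The case against.** There is a serious case on the other side, and much of it limits the point.

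- **Baseline weights are not given.** That FTC starts heavier than the literature cohorts is inferred from its description. Near the BMI 35 bound, at 1.70 m, an FTC member weighs about the assumed comparator mean and the gap vanishes. This stands: the figures illustrate and do not estimate.
- **The quantified effect is entirely one of scale.** It arises from comparing kilograms where percentages would give zero. This stands. No figure is available for any case-mix difference that would survive a relative scale.
- **The direction is not certain.** Very restricted physical capacity could reduce FTC's loss and reverse the bias. This stands.
- **The test may not be FTC-only.** The t-probability is attached to the study data just after the cohorts are said to be combined, the FTC sentence is permissive, and the control term in the FTC contrast is not defined as the literature curve. In a combined analysis the distortion is negligible. This stands for the combined comparison. It does not help an FTC trajectory set against the same curve, which the article allows.

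A reader might also infer that the whole FTC assessment depends on these benchmarks, or that all three were designed for the general programme. The documents support neither. The primary hypothesis is a within-person loss of at least 5% of baseline weight, which starting weight does not inflate in this way. FTC also has medical-record outcomes, and the Discussion offers no weight change as a plausible counterfactual. Only the survey and control-arm benchmarks are tied to the general programme.

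What remains is that no stated benchmark conditions on starting weight or BMI, and the group it may be used for is defined by severe obesity.

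**Conclusion.** The point holds as a limited one that should be put right. As written, an FTC difference from the literature curve in kilograms cannot be separated from a difference in starting weight. If FTC averages 120 to 150 kg against 100 kg and both lose 3%, the artefact is 0.6 to 1.5 kg, and an FTC-only test at n = 50 would favour FTC spuriously about 7% to 27% of the time against a nominal 2.5%. That rests on assumed weights, SDs and curve precision, and on loss proportional to weight. It is a possible bias, not a demonstrated one. It does not touch the 5% criterion, and it is close to nil if the formal test is made only on the combined cohorts.

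**What to change.** - Express both the study data and the literature curve as percentage (or log-ratio) change from baseline, using the mean baseline weights of the studies already reviewed. This removes the artefact quantified above.
- Compare FTC and general members with the curve separately.
- Where the studies' baseline weights or BMIs cover the FTC range, add baseline weight or BMI as a moderator, at least as a sensitivity analysis, and predict at each cohort's own mean. With at most 18 studies this is a between-study association and should be read with that caution.
- Where they do not cover it, say so and report FTC against the literature descriptively, without a t-probability.
- Label the ethnic, gender and age survey benchmark as context for FTC and not as its control.

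The cost is extraction of baseline means from papers already in hand and a refit of the meta-regression, with no new participants or measurements. The price is wider predicted intervals, the possible loss of studies that report no baseline weight, and perhaps no formal FTC comparison.
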